#### Secondary target variables

All secondary target variables, such as frequency, average and standard deviation will be tabulated per point of time (baseline, 6 weeks, 6 months) and per treatment arm. The historical data for ODI, MCS of SF-36 of PCS of SF-36 will be expressed as AUCs (areas under the curve) adjusted for the observation period. Once the data have been collected after 6 weeks, 6 months and 36 months, the missing values, if any, will be interpolated after 12 or 24 months, or the AUC will not be evaluated. The two-sided t-test for independent samples will be used to compare the intervention group with the control group. The Logrank test will be used to compare the treatment groups in terms of survival time to instability measured by the Kaplan-Meier method. The link between time to instability and the ODI will be investigated by correlation analysis. Following evaluation of the primary endpoint, the ITT population and the PP population – as sensibility analysis – will be analysed.

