## Methods and design

The study is a randomized, parallel-group, therapy-controlled trial in a clinical setting at two university hospitals. Outpatients presenting with degenerative disc disease, symptomatic facet joint arthrosis or spondylolisthesis will be assessed for inclusion. They will be asked to give an informed consent and will be randomized before surgery. Follow-up examinations will take place immediately after surgery, and after 6 weeks, 3 months and 6 months, the total duration of the study. Furthermore data will be assessed after 12, 24 and 36 months for a supplemental investigation. A further assessment will be performed every year, as it may be impossible to pronounce on ASD after 36 months.

This trial has received the approval of the ethics committee of the medical faculty of the University of Cologne under the reference number 12–231. The Clinical Trial Centre of the University of Cologne will monitor and manage the data. The research will be carried out in compliance with the Helsinki Declaration [21].

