### Outcome measures and assessments

#### Primary outcome measures

This investigation focusses on the subjective and objective clinical benefits for the patient. The ODI scores will be used to evaluate the functional outcomes after 6 weeks and after 6, 12, 24 and 36 months after surgery. The study hypothesis is:

The improvement in ODI scores from baseline to 6 months after surgery is clinically superior in the group with D-Rod (μRod) compared with the group without D-rod (μ).

To prove it, the following null hypothesis must be rejected: H0: |μRod - μ| ≤ MCID;

The alternative hypothesis is: H1: |μRod - μ| > MCID, with MCID assigning for minimum clinically important difference.

The hypothesis will be tested using a two-sided t-test for independent samples with a significance level of 5%.

In accordance with the recommendations of the European Agency for the Evaluation of Medicinal Products (EMEA), the patient’s bodily function may not be impaired if the only medical benefit is to relieve pain [25].

The ODI (cross-cultural adaption of the ODI version 2.1 for use with German-speaking patients) is a standardized, condition-specific questionnaire that gives a subjective percentage score of level of function (disability) in 10 everyday activities of daily living to be completed by patients rehabilitating from low back pain [25].

In the past, spine surgery investigations have focused on technical outcomes; now the main interest has turned to clinical outcomes [26, 27], measured by the ODI and SF-36™ , as in recent important trials (RCTs) [28, 29]. Radiologic findings are poor indicators of clinical outcome as it is unclear whether they correlate with clinical success.

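### The rule for the long-term ODI and SF-36 AUCs excludes any patient without a 36-month score, so that comparison is a complete-case analysis at odds with the ITT population named beside it

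*Protocol article*

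**What the plan says.** All of the AUC rule stands in the protocol article, Data analysis, *Secondary target variables*.

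- **Summary measure.** ODI and the two SF-36 component scores "will be expressed as AUCs (areas under the curve) adjusted for the observation period".
- **Gaps.** The article says that "the missing values, if any, will be interpolated after 12 or 24 months, or the AUC will not be evaluated". No interpolation method is named.
- **Condition.** That handling of gaps is tied to three visits by the opening words of the sentence: "Once the data have been collected after 6 weeks, 6 months and 36 months".
- **Test.** "The two-sided t-test for independent samples will be used to compare the intervention group with the control group".
- **Population.** "the ITT population and the PP population – as sensibility analysis – will be analysed". No other sensitivity analysis is stated.

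Elsewhere, *Primary outcome measures* sets the visits: "The ODI scores will be used to evaluate the functional outcomes after 6 weeks and after 6, 12, 24 and 36 months after surgery". *Methods and design* gives 6 months as the length of the study proper and adds: "Furthermore data will be assessed after 12, 24 and 36 months for a supplemental investigation". *Biases* states that there is no blinding.

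**The concern.** The rule makes three visits compulsory and two optional. A patient who misses month 36 gets no AUC, whatever was recorded at 12 and 24 months. A missing 6-week or 6-month score has the same effect. Scores already collected are discarded, and inclusion in the comparison depends on attendance up to three years after randomisation.

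The AUC is the only group comparison of these scores that the section expressly carries to 36 months. The *Discussion* calls prevention of adjacent segment disease the crucial question, and *Methods and design* doubts that even 36 months is long enough to judge it. The long-term scores therefore matter to the trial's purpose.

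Return could plausibly differ by arm. Patients know their treatment, the *Discussion* expects a larger surgical approach in the hybrid arm, and the *Background* cites a randomised trial with more implant failure after hybrid fixation. If return depends on how patients fare, and does so differently in the two arms, the AUC contrast no longer estimates the effect in the randomised groups.

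**Working it through.** **1. The plan's own figures.** Inputs from *Sample size*: SD 11.3, difference 11, two-sided 5%, power 80%, drop-out 10%. The exact t-test solution is 17.58 per arm, rounded up to 18 (power 81.0%), so 36 in total. Then 36 / 0.90 = 40. Both stated figures reproduce. They concern the 6-month test, and the article gives no loss rate to 36 months.

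**2. Who gets an AUC.** On the per-patient reading:

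| Scores present (besides baseline) | AUC? |
|---|---|
| 6 wk, 6, 12, 24, 36 mo | yes |
| 6 wk, 6, 36 mo and one of 12 or 24 | yes, gap interpolated |
| 6 wk, 6, 36 mo only | unclear (the text says 12 *or* 24) |
| 6 wk, 6, 12, 24 mo | no |
| 6, 12, 24, 36 mo | no |

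In the fourth row a time-averaged score over 0-24 months could be formed, and an adjustment for observation period would seem to allow it. The rule nevertheless drops the patient.

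**3. How many could be lost.** Take 36 patients at 6 months and assume a constant further yearly loss r over the remaining 2.5 years: n = 36 × (1 − r)^2.5.

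- r = 5%: 36 × 0.880 = 31.7
- r = 10%: 36 × 0.768 = 27.7
- r = 15%: 36 × 0.666 = 24.0

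So about 32 to 24 of 40 would have an AUC, and roughly 20-40% would not. The yearly rates are assumptions.

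**4. Possible bias.** Let d be the share of an arm without a 36-month score, and D the mean AUC (per unit time, in ODI points) of non-returners minus that of returners. The mean among returners is the arm mean minus d × D, so the bias in the contrast between arms A and B is −(dA·DA − dB·DB). All inputs are assumed.

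| dA, dB | DA, DB | Bias (ODI points) |
|---|---|---|
| 30%, 30% | 10, 10 | 0 |
| 20%, 10% | 10, 10 | −1.0 |
| 30%, 10% | 10, 10 | −2.0 |
| 40%, 20% | 10, 0 | −4.0 |

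For scale, the planned 6-month difference is 11 points.

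**5. What interpolation does.** Assume linear interpolation and a trapezoid AUC from baseline over 36 months, with 6 weeks taken as 1.5 months.

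- All visits present: weight of month 6 = (4.5/2 + 6/2)/36 = 14.6%; weight of month 36 = (12/2)/36 = 16.7%.
- Months 12 and 24 both filled in: month 6 = (4.5/2 + 30/2)/36 = 47.9%; month 36 = (30/2)/36 = 41.7%.

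Interpolation therefore reweights the observed scores. In the second case two readings supply about 90% of the summary (47.9% + 41.7% = 89.6%).

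**The case against.** **The sentence is ambiguous.** It could mean that the whole AUC analysis is abandoned if the data are incomplete. That reading is possible but less natural, and it would leave no expressly specified 36-month comparison of these scores. The sentence needs rewriting either way.

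**ITT with missing outcomes is not a strict contradiction.** Every trial that names an ITT population has some missing values. This stands in part. Here, however, the plan fixes a rule that removes patients who do have scores, and its only stated sensitivity analysis is per-protocol.

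**The data are supplemental.** The 12-36 month visits lie outside the 6-month study proper, and the primary test does not use this rule. This stands and limits the weight of the point.

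**Stronger readings that the documents do not support:**

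- *The comparison is biased by who returns.* Bias is a risk, not a result. Step 4 gives zero when the non-return share and the gap are equal in both arms.
- *Gaps are filled with straight lines, so most of the curve can be invented.* No method is named. If it is linear, a trapezoid AUC already runs straight between visits in complete data, so the length interpolated does not measure invented data.
- *The t-test understates uncertainty.* Each patient contributes one value and the test uses the observed spread of those values. Interpolated points do not add to n.
- *The later data go unsummarised.* Secondary variables "will be tabulated per point of time (baseline, 6 weeks, 6 months) and per treatment arm", which matches the stated 6-month duration. Tables for the supplemental phase may be left to the full protocol.
- *The t-test is wrong without baseline adjustment.* In a randomised comparison this is mainly a matter of precision.

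**Conclusion.** The point holds for the AUC comparison of ODI, PCS and MCS. Read per patient, the rule requires the 6-week, 6-month and 36-month scores, discards collected data when one is absent, and so makes the long-term t-test a complete-case comparison. That is at odds with the ITT population and fits poorly with the adjustment for observation period, both in the same section.

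The number excluded and the size of any bias cannot be derived from the document. Under the assumed yearly losses of 5-15%, 8 to 16 of 40 patients would have no AUC. Under the assumed unequal scenarios the bias is 1 to 4 ODI points; under equal ones it is zero.

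The point does not reach the primary result: the 6-month ODI test follows a separate rule. It should be corrected because it governs the long-term evidence on clinical scores and is cheap to put right.

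**What to change.** Replace the AUC t-test as the main long-term analysis. Suggested wording:

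> ODI, PCS and MCS will each be analysed in all randomised patients with a mixed model for repeated measures, using every available score at 6 weeks and at 6, 12, 24 and 36 months. The model will contain baseline score, centre, treatment, visit and treatment-by-visit. The time-averaged treatment difference will be a weighted contrast of the visit means. A patient will not be excluded for missing a particular visit.

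Possible contrast weights are the trapezoid ones over 0-36 months: 0.083, 0.146, 0.250, 0.333 and 0.167 for the five visits. The remaining 0.021 falls on baseline, where the adjusted difference is zero. With about 40 patients, an unstructured covariance for five visits has 5 × 6 / 2 = 15 parameters, so a simpler fallback structure should be fixed in advance.

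Keep the interpolated AUC as a sensitivity analysis. Name its interpolation method, and say whether 12 and 24 months may both be missing.

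The cost is wording and a little programming. No new data are needed: the scores are already scheduled, and centre is already a randomisation stratum. The model assumes data missing at random, so it does not remove bias from non-return that depends on unseen scores, and a patient with no score after baseline adds nothing to the estimate. It does use the scores that the present rule throws away.

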### Secondary outcome measures

PCS of the SF-36™. The SF-36™ is the most frequently used generic health status measure worldwide that includes parameters such as pain and walking distance. It has been further developed to comprise physical (PCS) and mental health (MCS) component scores, thus easing the interpretation and cross-cultural comparison. It is a standardized questionnaire used to evaluate the patients’ health-related quality of life. It yields an 8-scale profile of functional health and well-being scores, as well as psychometrically based physical and mental health summary measures, and a preference-based health utility index. Thus, the SF-36™ is a good measure of primary endpoint. The patients' answers are scored and added together to yield a sum total. The SF-36™ PCS scores of the experimental and control groups will be compared to further quantify patient outcomes. In the subsequent follow-ups, the SF-36™ will be repeated to detect any clinical impairment and/or clinical or radiologic instability. This follow-up will continue for up to 3 years and then each year after surgery. In cases of impairment, X-ray is indicated at any point of time. In total, MCS and 8 individual dimensions and subscales of the SF-36™ (version 4.0) are used to confirm and clarify the primary outcome results.COMI questionnaire (2008 version) - a short, patient-oriented, multidimensional outcome instrument validated for patients with spinal disorders.X-rays will be taken after 6 weeks, and after 6, 12, 24, and 36 months. A further assessment will be performed every year. These are common intervals after surgical implantation without extraneous radiation. If adjacent instability is discovered on a X-ray, the clinical outcome will be reevaluated. The criteria for both radiologic ASD and adjacent instability are listed in the Appendix (definition of radiologic instability and Weiner’s classification). Experienced radiologists will evaluate the pre- and postoperative X-rays to calculate the score in Weiner’s classification. Furthermore, after 6 months, full-length X-rays of the spine will be taken to assess sagittal balance parameters (pelvic incidence, sacral slope, pelvic tilt, lumbar lordosis, C7 plum line, SVA). At each follow-up visit, bone fusion will be evaluated by indirect signs (screw loosening, implant failure, loss of reduction).Clinical ASD will be assessed (see definition in the Appendix).Work disability at the time of and after surgery, and duration until return to work. At each visit, patients will be asked to grade their disability, and whether or when they have returned to work.Inpatient mortality and mortality at 6 months.Surgery-related data (blood loss, length of incision, duration of surgery) will be taken from the surgical report.During the study, type and dose of pain medication administered to the patients will be documented. If the patient complaints of pain, the medication will be adjusted. The adjustment will be recorded on the CRF.Intraoperative and postoperative complication rate (e.g. implant failure- see Appendix under “Safety”)Adverse Events (AE) and Serious Sdverse Svents (SAE) will be monitored and documented throughout the study (see Appendix under “Safety” and “AE and SAE”).

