
### Sample size

On the basis of the data provided by Parker et al., the standard deviation is set at 11.3 points and the minimal clinically relevant difference at 11 for the changes in the Oswestry Disability Index (ODI) scores between the baseline and six months. In order to detect this clinically relevant difference between the two treatment groups, using a two-sided t-test with a significance level of 5% and a power of 80%, a total of 36 patients is required (18 per group) [30].

Assuming a drop-out rate of 10% until follow-up, 40 patients must be recruited for the study.

At a recruitment rate of 50% of the eligible patients and a rate of 60% of eligible patients in the screened population, 80 patients must be eligible among the 133 screened patients.

At a screening rate of approx. 100 patients in 12 months, duration of recruitment would be 16 months. To comply with the CONSORT requirements, we will provide a flow diagram of the participants. For each group, it will show the numbers of participants who were randomly assigned, received intended treatment, and were analysed for the primary outcome. Furthermore a diagram will illustrate for each group, losses and exclusions after randomization, together with reasons [31].

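### Duration until return to work is a censored time, but the plan prescribes averages for it, leaves the scope of the t-test open and keeps Kaplan-Meier and log-rank for instability only

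*Protocol article*

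**What the plan says.** The protocol article lists as a secondary outcome "Work disability at the time of and after surgery, and duration until return to work" (*Secondary outcome measures*). It adds how this is collected: "At each visit, patients will be asked to grade their disability, and whether or when they have returned to work". The plan therefore expects that some patients will not have returned at a given visit.

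The analysis is described in *Secondary target variables*:

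- Description: "All secondary target variables, such as frequency, average and standard deviation will be tabulated", by arm, at baseline, 6 weeks and 6 months.
- Areas under the curve are formed for the ODI and the two SF-36 component scores.
- Directly after this: "The two-sided t-test for independent samples will be used to compare the intervention group with the control group". The sentence names no variable.
- Then: "The Logrank test will be used to compare the treatment groups in terms of survival time to instability measured by the Kaplan-Meier method". No other variable is given a time-to-event method.

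No sentence names a comparison for return to work or says how patients still off work enter a summary. *Methods and design* gives 6 months as the study duration, with supplemental data at 12, 24 and 36 months.

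**The concern.** For a patient still off work at 6 weeks or 6 months, the duration until return is not yet known; it is only known to exceed the time observed. An average duration at that visit can be formed in two ways. Either the patient is left out, and the arms are compared in subsets selected by the outcome itself, or a value is inserted, for which the article gives no rule.

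If patients are left out, the arm in which fewer return can look as fast as the other. The comparison is then no longer between the randomised groups, which sits badly with the intention-to-treat principle that the article adopts. The plan already contains the suitable method but gives it to a different variable.

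**Working it through.** **1. The plan's own figure.** *Sample size* gives SD 11.3, difference 11, two-sided 5% and 80% power for the ODI change. The normal approximation gives 2 × (1.960 + 0.842)² × (11.3/11)² = 16.6, so 17 per arm. The exact t-test solution is 17.6, so 18 per arm and 36 in total (power 0.81). With 10% drop-out, 36/0.9 = 40. The plan's figures reproduce. The article gives no figure for return to work, so the return rates below are assumptions.

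**2. Set-up.** Exponential times to return with a true ratio of medians of 2; 18 per arm, all in work before surgery; follow-up to F = 6 or 36 months with no other losses. For median m and λ = ln 2/m:

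- proportion returned by F: 1 − 0.5^(F/m)
- mean among returners: 1/λ − F·e^(−λF)/(1 − e^(−λF))

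Example, F = 6:

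- m = 6: 1/λ = 8.656, 50% returned, mean 8.656 − 6 × 0.5/0.5 = 2.66 months.
- m = 3: 1/λ = 4.328, 75% returned, mean 4.328 − 6 × 0.25/0.75 = 2.33 months.
- Ratio 2.66/2.33 = 1.14, where the medians differ twofold.

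**3. Results to 6 months.** Returned proportions and means follow from the formulas. Power is from 3,000 simulated trials per row (Monte Carlo standard error at most about 1 percentage point).

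| Medians (months) | Returned | Mean among returners | Ratio | t-test, returners only | t-test, non-returners set to 6 | Log-rank |
|---|---|---|---|---|---|---|
| 3 vs 1.5 | 75% / 94% | 2.33 / 1.76 | 1.32 | 15.8% | 42.5% | 47.0% |
| 6 vs 3 | 50% / 75% | 2.66 / 2.33 | 1.14 | 7.2% | 30.7% | 35.0% |
| 8 vs 4 | 41% / 65% | 2.74 / 2.49 | 1.10 | 6.4% | 26.9% | 32.0% |
| 12 vs 6 | 29% / 50% | 2.83 / 2.66 | 1.06 | 5.7% | 21.4% | 24.1% |
| 18 vs 9 | 21% / 37% | 2.88 / 2.77 | 1.04 | 5.1% | 15.6% | 18.9% |

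**4. Results to 36 months.**

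| Medians (months) | Returned | Ratio of means | t-test, returners only | t-test, non-returners set to 36 | Log-rank |
|---|---|---|---|---|---|
| 3 vs 1.5 | 100% / 100% | 2.00 | 48.8% | 48.8% | 52.7% |
| 6 vs 3 | 98% / 100% | 1.87 | 44.3% | 47.9% | 51.5% |
| 8 vs 4 | 96% / 100% | 1.73 | 40.8% | 49.9% | 52.9% |
| 12 vs 6 | 88% / 98% | 1.51 | 27.2% | 45.6% | 49.2% |
| 18 vs 9 | 75% / 94% | 1.32 | 17.6% | 43.5% | 47.4% |

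**5. Reading the tables.** The harm comes from dropping non-returners. Setting them to 6 months costs only about 3 to 5 percentage points of power against log-rank. The result is then a restricted mean, not a mean duration until return: for medians 6 vs 3 it is 0.5 × 8.656 = 4.33 against 0.75 × 4.328 = 3.25 months. With 36 months of data the loss is small when return is quick, but it persists when medians are long.

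**6. What log-rank can deliver.** For a hazard ratio of 2 at 80% power, Schoenfeld's formula needs 66 events and Freedman's 71. With medians 6 vs 3 and 6 months of follow-up, 18 × (0.50 + 0.75) = 22.5 events are expected. Log-rank is therefore underpowered too.

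**The case against.** A reader might infer that the plan compares duration until return to work by t-test and ignores patients who have not returned. The documents support neither statement.

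- The t-test sentence names no variable and stands directly after the area-under-the-curve sentences, so it may cover only the ODI and the two SF-36 component scores. Read as covering everything, it would also apply to mortality and complication rates, which is implausible.
- No section says that durations are averaged over returners only. Non-return is recorded at each visit, and the intention-to-treat population is named.

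It can also be said that the descriptive sentence lists frequencies next to averages for a mixed set of variables. The frequency of having returned is a sound summary and may be what is meant. Seen this way, only a missing test and censoring rule for one of many secondary outcomes remains, and an article may leave those to the full protocol or analysis plan. The simulated contrast also depends on assumed return rates and on the 6-month cut-off.

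Most of this stands, and it limits the point. What does not fall away is the text itself. It applies averages to all secondary variables at fixed visits up to 6 months, and it assigns the survival method to one time-to-event outcome while another is listed. An analysis plan that followed this wording would need either a selected subset or an unstated imputation to produce an average duration. That is an ill-fitting choice on the page, not only an absent detail.

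**Conclusion.** The point holds as a minor one. The prescribed summary does not fit a censored duration, the scope of the t-test is unclear, and the suitable method is already in the plan for instability.

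Its size is conditional. Only if durations are averaged over returners at 6 months does a twofold difference in medians shrink to a ratio of 1.04 to 1.32, with the power loss shown above. This rests on exponential times, the assumed medians and all 18 patients per arm being in work before surgery. If some were not, fewer patients would contribute and power would be lower for every method.

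The change would not make this a powered comparison. The gain is mainly an unbiased description and comparison of the randomised arms. The primary ODI analysis is not affected.

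**What to change.** In *Secondary target variables*:

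1. State that duration until return to work is analysed by Kaplan-Meier and the log-rank test among patients in work before the illness or surgery, with patients who have not returned censored at last contact.
2. Report the proportion returned at each visit instead of a mean duration.
3. State which variables the t-test covers.

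The cost is two or three sentences. The method is already planned for instability, and whether and when patients return is already asked at each visit. The one item to confirm is that the case report form identifies who was in work beforehand; the article mentions work disability at the time of surgery but does not show the form.

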Another issue is whether the radiographically detectable adjacent degeneration is an indicator of clinical outcome. As already mentioned, spinal fusion creates increased strain on adjacent levels and can result in ASD. Adjacent instability has been reported even 6 to 12 months after surgery [3, 14], with varying average rates. In a retrospective study, Cheh et al. identified radiographic ASD in 42.6% of the patients (average follow-up of 7.8 years). Oswestry scores were worse in patients with radiographic ASD. Clinical ASD developed in 43% [3]. Other authors reported an incidence of ASD of up to 24% (average follow-up of 39 months). In that study, instability developed more frequently above the fusion [14]. Yang et al. found a significant correlation between clinical outcome and ASD [15]. In a 30-year follow-up comparing patients undergoing various spinal procedures (fusion, discectomy, decompression), Kumar et al. [16] found that the incidence of radiographic changes in levels above the operated region was twice higher after fusion than after the other procedures. In contrast, validated scales and functional testing (e.g. SF-36) showed no significant differences in outcome. The authors concluded that radiographic changes do not necessarily lead to functional impairment in all patients. Other evidence suggests that radiologic degeneration of the superior adjacent segment does not correlate with clinical results [17]. Ghiselli et al. reported an adjacent segment disease rate of 16.5% after 5 years in a collective of 215 patients who had undergone lumbar spine arthrodesis. This rate went up to 30.1% at ten years follow-up [18]. However, a previous review mentions a correlation between fusion and adjacent segment degeneration compared to arthroplasty. This correlation appears to be even stronger if adjacent segment disease is observed, thus underlining the impact of fusion on the adjacent segments [2]. In this context, sagittal imbalance is another factor of considerable importance; some studies indicate that it favours the development of the disease [19, 20].

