### Objective

The objective of the study is to address the following questions:

Does posterior hybrid stabilization with a new topping off device lead to a better or at least equivalent clinical outcome compared to standard fusion? Clinical outcome assessment will be performed using ODI, SF-36 and COMI questionnaires.

Does it prevent adjacent instability/segment disease?

Does radiographic ASD correlate with clinical outcome?

Does this new device lead to a higher complication rate (e.g. implant failure) than standard fusion?

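### Study question 3 is to be answered by correlating ODI with a mostly censored time to instability, which would mainly dilute any real association

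*Protocol article*

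**What the plan says.** The Objective section of the protocol article lists four questions. The third is: "Does radiographic ASD correlate with clinical outcome"

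The matching analysis stands under Data analysis, Secondary target variables: "The link between time to instability and the ODI will be investigated by correlation analysis". The sentence before it reads: "The Logrank test will be used to compare the treatment groups in terms of survival time to instability measured by the Kaplan-Meier method". So the variable is handled as survival time when the arms are compared, and as one member of a correlated pair when it is related to ODI.

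Both measures are scheduled for every patient at the same visits. On X-rays, under Secondary outcome measures: "X-rays will be taken after 6 weeks, and after 6, 12, 24, and 36 months". On ODI, under Primary outcome measures: "The ODI scores will be used to evaluate the functional outcomes after 6 weeks and after 6, 12, 24 and 36 months after surgery".

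The Secondary outcome measures section also provides for two kinds of extra contact. One is prompted by the patient's state: "In cases of impairment, X-ray is indicated at any point of time". The other is prompted by a film: "If adjacent instability is discovered on a X-ray, the clinical outcome will be reevaluated".

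**The concern.** Time to instability is known only for patients who become unstable. For the rest, the data say only that it exceeds their follow-up. Kaplan-Meier and the log-rank test take this into account. A correlation coefficient, as ordinarily understood, does not. Whoever runs it has two obvious options:

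- keep only patients with an event, which discards most of the trial and selects on the outcome;
- enter the censoring time as if it were the event time, which gives most patients nearly the same value and makes the coefficient depend partly on length of follow-up.

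At stake is the answer to one of the four stated questions. The likely error is a weak or null correlation, read as evidence that radiographic change does not matter clinically, when the method could hardly have shown otherwise. A second and smaller worry is that X-rays prompted by impairment, and re-evaluations prompted by X-rays, could tie the two measures together if their data enter the analysis.

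**Working it through.** **1. Number of patients.** The Sample size section gives SD 11.3, difference 11, two-sided 5%, power 80%, 36 analysed and 40 recruited. This reproduces: the t-test needs 17.58, so 18 per arm, and 36 / 0.90 = 40. The figure is for the primary comparison. The article gives no event count or power for the link between instability and ODI.

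**2. Expected events by 36 months.** The Background cites several rates, among them: "Other authors reported an incidence of ASD of up to 24% (average follow-up of 39 months". Under a constant hazard (my assumption), P(event by 36 months) = 1 - (1 - p)^(36/t), where p is the rate cited at t months.

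| Cited rate | Calculation | Event by 36 months | Of 36 | Of 40 |
|---|---|---|---|---|
| 16.5% at 5 years | 1 - 0.835^(36/60) | 10.3% | 3.7 | 4.1 |
| 42.6% at 7.8 years | 1 - 0.574^(36/93.6) | 19.2% | 6.9 | 7.7 |
| 24% at 39 months | 1 - 0.76^(36/39) | 22.4% | 8.1 | 9.0 |

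Between 78% and 90% of times are therefore censored at 36 months. For half the patients to have an event by then, the hazard would have to be ln 2 / 3 = 0.231 per year. The highest cited one is -ln(0.76) / 3.25 = 0.084 per year, so the ratio is about 2.7.

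**3. Effect of an ordinary correlation when a link exists.** Simulation with n = 36, Spearman correlation, X-rays at the protocol visits, and hazard ratio 2 per SD of ODI (assumed). The uncensored correlation is about -0.48.

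- Censoring times counted as event times: mean -0.19 with a 10% baseline event rate, -0.27 with 22%.
- Patients with events only: mean -0.02 to -0.07. At the 10% rate, 35% of trials had fewer than four events or no spread in times.

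A second set-up (latent correlation -0.5, continuous times) gave -0.28 to -0.36 for the first coding without dropout, and -0.13 to -0.22 with 30% dropout unrelated to ODI. Events-only gave about -0.17 to -0.22 with SD 0.4-0.5. The amount of dilution depends on the set-up; its direction does not.

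**4. Effect when no link exists.** Censoring times counted as event times, ODI taken as available for everyone:

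- Dropout unrelated to ODI, up to 30%: mean correlation about 0, significant in 4-6% of trials.
- Dropout 10% (the protocol's figure), with an assumed log-odds of 1 per SD of ODI: mean about -0.11 to -0.17, significant in about 12-18%.
- Dropout 30% with the same dependence: significant in roughly 24-48%, depending on event rate and coefficient. Both the rate and the dependence are assumptions here.

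**5. Effect of triggered X-rays when no link exists.** Extra films for the worst ODI quartile, same coding: mean correlation about -0.02 with error-free readings, and -0.07 to -0.08 with an assumed 3% false positives per film. Rejection rate 4-8% against a nominal 5%. Events-only gave means of -0.05 to -0.10.

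**6. What a suitable method could deliver.** A Cox model with hazard ratio 2 per SD needs (1.96 + 0.84)^2 / (ln 2)^2, about 16 to 17 events, for 80% power. With 4 events power is about 28%, with 8 about 50%. A simple contrast of ODI (difference 11, SD 11.3, normal approximation) has about 45% power for 4 against 32 patients and 68% for 8 against 28.

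**The case against.** The article names no coefficient and does not say how event-free patients enter. The authors plainly know that this is survival data, and an analysis plan that is not shown could set a method that allows for censoring. So the two codings tested above are readings of the sentence, not quotations from it. That stands, and it rules out saying that the result will certainly be wrong. It does not remove the point: a correlation is the stated method, and taken in its usual sense it does not fit the variable.

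The event rates are borrowed. They describe ASD in other populations, not instability as the Appendix defines it, and patients here must already have adjacent degeneration, so the true rate may be higher. Yearly follow-up also continues past 36 months. This too stands. Yet even at 7.8 and 10 years the cited rates (42.6% and 30.1%) leave 57-70% of patients event-free.

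A reader might infer more: that the association is partly built in, because impairment and X-ray findings prompt each other's assessment. The document does not support this. Every patient has scheduled films and ODI at the same visits, and the Biases section assigns the questionnaire survey and the X-ray evaluation to different physicians. The sentence on impairment follows the repeated SF-36, not the ODI. Nothing says that a re-evaluation replaces the scheduled ODI value. The simulated effect of triggered films is small.

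A reader might also infer that dropout will produce frequent false positives. That requires dropout that depends on ODI, which no section states, together with the naive coding. The larger percentages also need about 30% dropout, against the 10% that the protocol assumes.

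**Conclusion.** The point holds as a stated method that does not suit its variable. On the document's own cited rates and a constant hazard, about 4-9 of 40 patients would have an event by 36 months and 78-90% of times would be censored. An ordinary correlation would mainly dilute a true association or rest on too few patients to interpret.

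A spurious correlation is a conditional risk only: about 12-18% significant results under no link, if 10% drop out with log-odds 1 per SD of ODI, and near 5% if dropout is unrelated to ODI. Triggered contacts may add a small further link if their data are used. It would go too far to say that the result will be biased or is partly built in.

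No method makes 4-9 events informative, so the answer to this question will be exploratory whichever analysis is chosen. The primary comparison is not affected.

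**What to change.** Replace the correlation sentence under Secondary target variables with wording to this effect:

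> The association between radiographic instability and ODI will be explored in a linear mixed model of ODI at the scheduled follow-up visits. Instability (present or absent by that visit) is a time-varying covariate, and baseline ODI, treatment, centre and visit are adjusted for. The main analysis uses ODI and X-rays from scheduled visits. Data from additional contacts prompted by impairment or by an X-ray finding are added in a sensitivity analysis. The result is exploratory because few events are expected.

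The number of patients with instability should be reported beside the estimate and its confidence interval.

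The cost is slightly more analysis work than a single coefficient. ODI and X-rays are already scheduled at the same visits, so no new data collection is needed. Precision will remain low.
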